**Figure 1 F1:**
[figure not shown]
Flowchart of participant journey through the feasibility study. ABR, annualised bleeding rate; HEAD-US, Haemophilia Early Arthropathy Detection with Ultrasound; HJHS, Haemophilia Joint Health Score; TUDS, timed-up-and-down-stairs; 6MWT, 6-minute timed walk.

It is impossible to blind those in receipt and those delivering the intervention as to the group allocation. However, it will be possible—although perhaps challenging—to blind the assessor as to group allocation. Consequently, we will attempt a single blind approach in which the participant and physiotherapists delivering the intervention will be encouraged to withhold their group allocation from the assessors collecting data. We will use a range of strategies, including instruction in the participant literature, intervention protocol and with frequent verbal prompts. In order to assess the efficacy of blinding, we will ask assessors to record which group they think participants have been allocated to at the end of each assessment. This will be presented as a binary forced choice. There are no circumstances under which it would be necessary to unblind assessors.

### Intervention

The intervention developed by expert clinicians and patients utilising a modified Nominal Group Technique (NGT) is a 24-session, 12-week programme designed as 2-week progressive levels (intensity and or load) with no more than 10 exercises in each session, taking 25–30 min to complete (figure 2). The intervention aims to master movement control and emphasises body-weight strength development. Pictures of the exercises and instructions for each phase will be provided in 2-week exercise diaries. Participants will be asked to complete the exercises twice per week; once with the physiotherapist who will visit the participant at home and once supervised by their parents/guardian. Completion of exercises, along with treatment regimen, any adverse events and comments in relation to the exercise programme will be recorded in the exercise diary. They will also record participation in physical activities, including type, time and intensity. According to predetermined criteria (safe and competent), the physiotherapist will determine if it is appropriate for the participant to progress to the next exercise level. On return of the exercise diary every 2 weeks, participants will be provided with a gift voucher.

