**Methods and analysis:**

A small-scale two-centre RCT of a 12-week muscle strengthening exercise intervention versus usual care for young children with haemophilia will be conducted. Primary outcomes will be safety and adherence to the exercise intervention. Secondary outcomes will include recruitment, retention and adverse event rates, clinical data, muscle strength, joint biomechanics and foot loading patterns during walking, 6 min timed walk, timed-up-and-down-stairs, EQ-5D-Y, participants’ perceptions of the study, training requirements and relevant costs. Recruitment, follow-up, safety and adherence rates will be described as percentages. Participant diary and interview data will be analysed using a framework analysis. Demographic and disease variable distributions will be analysed for descriptive purposes and covariant analysis. Estimates of differences between treatment arms (adjusted for baseline) and 75% and 95% CIs will be calculated.

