### Usual care

Participants will continue to receive their usual care as recommended and prescribed by the haematologist, physiotherapist and other members of the healthcare team. This will include factor concentrate treatment, any physiotherapy or surgical intervention or advice that is recommended by the clinical care team. There are currently no standardised treatment recommendations for children without apparent joint damage. The researchers will not make or initiate any changes to routine treatment. Any change to or initiation of new treatment or intervention will be recorded and the treating clinician will determine whether it is appropriate for the participant to continue in the study. Participants will be provided with a diary to record participation in physical activities, including type, time and intensity. Participants will be telephoned weekly to encourage dairy completion. On return of the diary every 2 weeks, participants will be provided with a gift voucher.

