### Outcome measures

Primary outcome measures are as follows:Safety will be evaluated using annualised bleeding rates, coagulation factor usage (what the patient actually administers and records on their routine electronic diary) and reported adverse events and reactions associated with the intervention. Association with symptoms of joint disease (Haemophilia Joint Health Score and Haemophilia Early Arthropathy Detection with Ultrasound score) will be evaluated.Adherence to the exercise intervention will be evaluated by the number of exercise session completed as a percentage of the prescribed exercise sessions. Data will be extracted from participant diaries.

Secondary outcome measures are as follows:Recruitment rate determined as the participants who volunteer to participate in the study as a percentage of those that are invited/eligible.Willingness to be randomised; evaluated at the end of study through semistructured interviews that will be audio-recorded and be transcribed by a member of the research team.Participant’s acceptability of the trial and intervention: using semistructured interviews, conducted at the completion of the study, the participants will be asked their views on acceptability of the trial and intervention, recruitment and exercise adherence. The interview will be audio-recorded and transcribed by a member of the research team.Training required to deliver the intervention and collect outcome data at study visits: using semistructured interviews, conducted at the completion of the study, the physiotherapists will be asked their views on acceptability of the trial and intervention, recruitment and exercise adherence. They will also be asked about the training requirements for delivering the intervention as well as the appropriateness of the outcomes piloted in terms of training, length of time to complete and clinical value of the data. The interview will be audio-recorded and transcribed by a member of the research team.Haemophilia Joint Health Score (HJHS)—a clinical examination of swelling, muscle atrophy, strength, joint crepitus, range of motion and pain at the ankle, knee and elbow joints. The HJHS is a standardised multi-item assessment, currently used in clinic as part of routine care to record musculoskeletal health.^22^

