### Management and oversight of the study

East Kent Hospital University Foundation Trust is the study sponsor. They have overall responsibility for governance of the study and have no direct role in study design, data collection, management, analysis, interpretation of data and reports and publications that arise from the study.

A Research Monitoring Committee (RMC) has been established and will meet 6 monthly after the study has commenced. The RMC will be responsible for monitoring milestones and targets, data, safety, recruitment, reviewing and interpreting the results. The RMC will be chaired by an independent chair from outside the research team group. Additional meetings may be called to review any serious adverse events, adverse events (AEs) and adverse reactions (ARs). The chief investigator will co-ordinate day to day running of the research, complete ethical approvals, communicate with recruitment sites, complete training of physiotherapists to deliver the intervention, undertake research initiation and monitoring site visits, co-ordinate data analysis and interpretation. The chief investigator will notify the RMC in the case of AEs and ARs. The principal investigator at each site will be the physiotherapist delivering the intervention. They will be responsible for recruitment and screening participants according to the inclusion and exclusion criteria, reporting AEs and ARs and local governance requirements.

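### Adverse events are prompted for in the exercise-arm diary but not, as described, in the usual-care diary, so adverse-event percentages by arm would be open to ascertainment bias

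*Protocol article*

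**What the plan says.** **Exercise arm (Protocol article, Intervention).** Besides exercise completion, the plan states: "along with treatment regimen, any adverse events and comments in relation to the exercise programme will be recorded in the exercise diary". The boys also log their physical activity. Sessions take place twice a week, "once with the physiotherapist who will visit the participant at home and once supervised by their parents/guardian".

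**Usual-care arm (Usual care).** "Participants will be provided with a diary to record participation in physical activities, including type, time and intensity". Contact is by telephone: "Participants will be telephoned weekly to encourage dairy completion". The section adds that changes to treatment, or new treatment, are recorded.

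**Outcome (Outcome measures).** Safety is a primary outcome with three components: annualised bleeding rate, factor usage, and "reported adverse events and reactions associated with the intervention". Factor usage is "what the patient actually administers and records on their routine electronic diary". The source of the bleeding-rate data is not named.

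**Reporting (Management and oversight of the study).** The site principal investigator reports adverse events and reactions, and no arm is excluded. However, "The principal investigator at each site will be the physiotherapist delivering the intervention", and Study design calls that person unblinded.

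**Analysis (Analysis methods).** Safety rates are given as percentages. The between-group analysis of covariance applies to change-from-baseline data and does not name adverse events.

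**Abstract.** "Secondary outcomes will include recruitment, retention and adverse event rates", whereas the body places adverse events under the primary safety outcome.

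**The concern.** A randomised control arm gives a useful reference for adverse events only if events are sought in the same way in both arms. Here one arm has a diary that asks for them and a weekly face-to-face visit. The other has a diary described without that item and a call with a different stated purpose. The reporter at each site sees the exercise boys at home and is not described as having equivalent contact with the controls.

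If the percentages are set out by arm, an excess under exercise could be real or could reflect better capture, and the data could not tell the two apart. The Introduction says it is unknown whether strengthening exercise helps or harms these children, so the safety percentages will be read closely. The study is also meant to inform the design of a definitive trial, and its adverse-event procedures could be carried forward.

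**Working it through.** The plan gives no capture rate, adverse-event rate or sample-size calculation on this point, so there is no figure to reproduce. The check has two parts.

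**1. Capture routes side by side**

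| Route | Exercise arm | Usual-care arm |
|---|---|---|
| Study diary | Exercise, treatment, adverse events, comments, physical activity | Physical activity |
| Weekly contact | Home visit by physiotherapist | Call to encourage diary completion |
| Diary return | Every 2 weeks | Every 2 weeks |
| Site reporting of adverse events | Yes, by the delivering physiotherapist | Yes (no restriction stated), by the same person |
| Factor usage | Routine electronic diary | Routine electronic diary (no restriction stated) |
| Bleeds | Source not named | Source not named |

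The arms differ on the first two rows. They are the same, or not shown to differ, on the rest.

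**2. How large the effect could be (illustration)**

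Inputs from the protocol: 20 boys allocated 1:1, so about 10 per arm; 12 weeks. Assumptions:
- The true event rate *r* is equal in the two arms, at 1 or 2 per boy-year. The Introduction gives this as the bleeding rate on prophylaxis. It is borrowed only as an order of magnitude for adverse events.
- Events follow a Poisson distribution.
- Capture is complete in the exercise arm and a fraction *c* of that under usual care.

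Formulas:
- Expected events in an arm of 10 = 10 × *r* × 12/52 × capture. With full capture this is 2.3 (*r* = 1) or 4.6 (*r* = 2).
- Apparent rate ratio = 1/*c*.
- Percentage of boys with at least one recorded event = 1 − exp(−*r* × 12/52 × capture).

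| *c* | Apparent ratio | *r* = 1: exercise vs usual care (gap) | *r* = 2: exercise vs usual care (gap) |
|---|---|---|---|
| 1.0 | 1.00 | 20.6% vs 20.6% (0) | 37.0% vs 37.0% (0) |
| 0.8 | 1.25 | 20.6% vs 16.9% (3.8) | 37.0% vs 30.9% (6.1) |
| 0.6 | 1.67 | 20.6% vs 12.9% (7.7) | 37.0% vs 24.2% (12.8) |
| 0.5 | 2.00 | 20.6% vs 10.9% (9.7) | 37.0% vs 20.6% (16.4) |
| 0.4 | 2.50 | 20.6% vs 8.8% (11.8) | 37.0% vs 16.9% (20.1) |

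Gaps are in percentage points, taken before rounding. One boy is 10 points in an arm of 10, so the spurious gap runs from 0.4 to 2.0 boys. With equal capture it is zero.

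The ratio column only restates the assumed capture fraction. It shows the direction and is not evidence of size.

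**The case against.** **No between-arm test of adverse events is planned.** This is true: safety is only described. It rules out saying that a planned comparison is biased. It does not remove the problem, because percentages shown by arm carry the same difference in capture with or without a test.

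**The safety wording may concern the exercise arm only.** The phrase "reported adverse events and reactions associated with the intervention" is ambiguous. If its ending covers both nouns, the component has no usual-care counterpart during the 12 weeks, and unequal diaries cannot bias it; but then the control arm gives no adverse-event reference. If the ending covers reactions only, all adverse events count and capture is unequal. A reader might infer that events judged unrelated drop out of the primary outcome. That follows on the first reading only, and the text does not settle which is meant.

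**Usual-care events are not lost.** This stands. Site investigators report events with no arm restriction, a monitoring committee with an independent chair oversees safety, and control families have weekly contact. What is not described is an equal prompt; a route exists.

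**Treatment and bleeds.** A reader might extend the point to these, since the exercise diary also lists treatment. The documents do not support that. The safety measure is factor usage, taken from the routine electronic diary with no arm restriction, and treatment changes are recorded under usual care. The source of bleed data is unnamed, so unequal capture is not shown.

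**The article condenses a fuller protocol (V.2).** The usual-care diary may hold more than is described. This lowers confidence. However, the article lists the contents of both diaries, describes the physical-activity item alike in each, and gives adverse events in one only.

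**Conclusion.** The point holds for the adverse-event component of the primary safety outcome, and only for that. As described, adverse events are prompted in one arm and not in the other, and the shared reporting route runs through an unblinded person with closer contact with the exercise arm. Adverse-event percentages by arm would therefore be open to ascertainment bias, most likely making exercise look less safe.

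The size is unknown. Under the assumptions above it is about 4 to 20 percentage points, or up to about two boys in an arm of 10. That range depends on an assumed usual-care capture of 40% to 80% relative to the exercise arm, on a bleeding rate borrowed as the event rate, and on the diary containing no more than the article says.

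It is a correctable weakness in data collection, and does not invalidate a feasibility study whose safety analysis is descriptive. The difference between abstract and body over whether adverse event rates are primary or secondary is real but minor, and adds nothing to the ascertainment argument.

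**What to change.** - Put the same adverse-event page in the usual-care diary as in the exercise diary.
- Ask one scripted adverse-event question, in the same words, at the weekly call and at the weekly home visit.
- Tabulate all adverse events by randomised arm whatever their attribution, with relatedness in a separate column. This also removes the ambiguity in the safety wording.
- Make the abstract agree with the body on the status of adverse event rates.

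If V.2 already provides the same page and question in both arms, a sentence saying so under Usual care is enough for the first two items.

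The cost is one extra diary page and one question per weekly contact. The weekly call and two-weekly diary return already exist in the usual-care arm, so no new contact is needed.

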**Figure 2 F2:**
[figure not shown]
Description of the exercise intervention.

### Usual care

Participants will continue to receive their usual care as recommended and prescribed by the haematologist, physiotherapist and other members of the healthcare team. This will include factor concentrate treatment, any physiotherapy or surgical intervention or advice that is recommended by the clinical care team. There are currently no standardised treatment recommendations for children without apparent joint damage. The researchers will not make or initiate any changes to routine treatment. Any change to or initiation of new treatment or intervention will be recorded and the treating clinician will determine whether it is appropriate for the participant to continue in the study. Participants will be provided with a diary to record participation in physical activities, including type, time and intensity. Participants will be telephoned weekly to encourage dairy completion. On return of the diary every 2 weeks, participants will be provided with a gift voucher.

### Outcome measures

Primary outcome measures are as follows:Safety will be evaluated using annualised bleeding rates, coagulation factor usage (what the patient actually administers and records on their routine electronic diary) and reported adverse events and reactions associated with the intervention. Association with symptoms of joint disease (Haemophilia Joint Health Score and Haemophilia Early Arthropathy Detection with Ultrasound score) will be evaluated.Adherence to the exercise intervention will be evaluated by the number of exercise session completed as a percentage of the prescribed exercise sessions. Data will be extracted from participant diaries.

Secondary outcome measures are as follows:Recruitment rate determined as the participants who volunteer to participate in the study as a percentage of those that are invited/eligible.Willingness to be randomised; evaluated at the end of study through semistructured interviews that will be audio-recorded and be transcribed by a member of the research team.Participant’s acceptability of the trial and intervention: using semistructured interviews, conducted at the completion of the study, the participants will be asked their views on acceptability of the trial and intervention, recruitment and exercise adherence. The interview will be audio-recorded and transcribed by a member of the research team.Training required to deliver the intervention and collect outcome data at study visits: using semistructured interviews, conducted at the completion of the study, the physiotherapists will be asked their views on acceptability of the trial and intervention, recruitment and exercise adherence. They will also be asked about the training requirements for delivering the intervention as well as the appropriateness of the outcomes piloted in terms of training, length of time to complete and clinical value of the data. The interview will be audio-recorded and transcribed by a member of the research team.Haemophilia Joint Health Score (HJHS)—a clinical examination of swelling, muscle atrophy, strength, joint crepitus, range of motion and pain at the ankle, knee and elbow joints. The HJHS is a standardised multi-item assessment, currently used in clinic as part of routine care to record musculoskeletal health.^22^
Haemophilic synovitis and arthropathy—the presence and severity of signs of haemophilic synovitis and arthropathy will be evaluated using the Haemophilia Early Arthropathy Detection with Ultrasound (HEAD-US) score. The HEAD-US protocol is a standardised scanning protocol used to identify the presence and severity of synovitis, articular cartilage and chondral bone defects in the ankle, knee and elbow joint. The scanning procedure takes approximately 2–3 min per joint and we have recently shown good inter-rater repeatability of this protocol when performed by physiotherapists.^23 24^
Muscle strength of the knee extensors and ankle dorsiflexors and plantarflexors—maximum torque will be recorded with a hand-held dynamometer (Manual Muscle Tester, Lafayette Instrument, USA) using our standardised protocol with excellent test-retest repeatability.^15^
Joint biomechanics and motion during walking—temporal spatial and three-dimensional (3D) joint motion during gait will be recorded using an inertial magnetic measurement gait analysis system (MVN BIOMECH Awinda, Xsens Technologies, Netherlands). Sensor units will be attached to the feet, lower legs, thighs and pelvis with elastic straps. Motion of the sensors will be used to calculate temporal spatial and 3D lower limb joint motion.Static and dynamic foot loading patterns—will be evaluated with a plantar pressure platform (HR Mat, Tekscan, USA). Centre of pressure motion in respect of distance and direction travelled, together with contact time as a measure of foot symmetry of foot loading for various foot segments (heel, midfoot and forefoot) along with distribution of peak pressure and pressure-time integrals will be evaluated.Six min timed walk—distance walked in 6 min. Two marker cones will be placed 30 m apart along a corridor and each subject will be asked to walk back and forth between the cones as fast as they can for 6 min.^15^
Timed-up-and-down-stairs—time taken to ascend and descend a flight of 12 steps. The children will stand 30 cm from the bottom step and asked to walk quickly but safely up the stairs, turn around on the top step and come all the way down until both feet land on the bottom step. They will be instructed to step on every step, use the hand rail if they want and not to run.^15^
EQ-5D-Y—a five dimension (mobility, self-care, usual activities, pain/discomfort, anxiety/depression) questionnaire measuring health-related quality of life.^25^
Costs relevant to the study—intervention costs, health and social care costs, out-of-pocket expenses and time off work costs. Healthcare costs (using National Health Service reference costs were possible) will include training and delivering the intervention, equipment, overhead costs, visits to hospital/haemophilia clinic, general practitioner, other healthcare services, investigations, hospitalisation, treatment, coagulation clotting factor concentrate and medication. Patient and family costs will include travel and time off work. Feasibility of collecting these data will be explored along with the resource consequences.

Data will be collected at the respective haemophilia centres. All data collected related to the study will be confidential and anonymous. The participant will be allocated a randomised participant number code, and all data collected will relate to this code. A record of which code belongs to which subject will be stored in a locked cabinet separate from the study data. Only the principle investigator (who will be a member of the participant’s direct care team) will have access to this documentation. The direct care team and the principal investigator will have access to participant’s personal and identifiable information during the study. Consent will be sought by the lead researcher for the research team to have access to this personal information.

